### Randomization

Samples will be selected through stratified sampling and random samples are then selected from each stratum. The strata consist of five cities, and separate randomization lists will be prepared for each city using a block randomization.

Due to the limited number of main public centers providing compulsory premarital counselling in each city (3 centers in Tehran, 2 centers in in Ahvaz, 1 center in Shiraz, 2 centers in Tabriz and 3 centers in Mashhad), and other concerns such as selection bias, and generalizability (according to potential confounder of socioeconomic status), the cluster randomization based on the centers is not possible. So, we will use central randomization that is stratified to the cities.

The PI will randomly assign the couples into two groups in each city by a computer-generated random sequence. For randomization, the permuted block randomization will be used (block size = 4). According to the sample size of 440 identified, 110 blocks will be produced using the online site (www.sealedenvelope. com) for Tehran. According to the sample size of 200 identified, 50 blocks will be produced using the online site (www.sealedenvelope. com) for other cities.

Allocation will be concealed by using sequentially numbered opaque sealed envelopes that contain group assignments determined by computer-generated random sequences.

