### Sample size

According to our primary outcomes including fertility knowledge and intention toward childbearing that are important to be measured 3 months after the intervention, we considered a small standardized Cohen effect size (d = 0.2) with a type I error of 5% (α = 0.05) and a type II error of 10% (β = 0.1; power = 90%) and sample size obtained 527 in each group and considering 15% of loss to follow up, the sample size was calculated 620 couples in each group using the G-Power software. Considering the design effect equals to 1.5, final size was calculated 1240 couples in total (620 couples in each group). In each city around 200 couples (100 in each group) and from Tehran about 440 couples (220 in each group) will be recruited.

It should be noted that in order to compare quantitative outcomes between groups over time (baseline, 3, 12 and 18 month), the sample size obtained 660 couples in total (330 in each group) based on repeated measures ANOVA. So, the initial obtained sample size (620 couples in each group) will have the appropriate power for this analysis.

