### Blinding

Given the nature of the intervention, it is not possible to blind participants to researchers involved in providing the intervention and data collection. However, allocation to intervention or control groups will be blinded for researchers in the data set available during the data analysis. To avoid the potential contamination between two groups, we will provide the educational intervention after the typical premarital counselling.

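### One fixed block size of 4 on every city list, in a trial whose field staff are unblinded, makes allocations more predictable than they need be

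*Protocol article*

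**What the plan says.** All of this stands in the protocol article.

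- **Lists.** Randomisation is stratified by city, with one list per city: "The strata consist of five cities, and separate randomization lists will be prepared for each city using a block randomization". The same section counts 3 centres in Tehran, 3 in Mashhad, 2 in Ahvaz, 2 in Tabriz and 1 in Shiraz, so four of the five lists serve more than one centre.
- **Block size.** "For randomization, the permuted block randomization will be used (block size = 4". The block counts confirm that the size does not vary: "According to the sample size of 440 identified, 110 blocks will be produced" for Tehran and "According to the sample size of 200 identified, 50 blocks will be produced" for each other city.
- **Ratio.** Sample size gives "final size was calculated 1240 couples in total (620 couples in each group", so each block holds two couples per arm.
- **Mechanism.** Randomization says "So, we will use central randomization that is stratified to the cities", then that the principal investigator assigns the couples, then "Allocation will be concealed by using sequentially numbered opaque sealed envelopes".
- **Blinding.** "it is not possible to blind participants to researchers involved in providing the intervention and data collection". The sentence is awkward. I read it as saying that neither participants nor these researchers are blinded, because the only blinding claimed is at data analysis.

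**The concern.** When blocks have one known size, the last allocation in each block is settled by those before it, and sometimes the third is too. Blinding would normally keep past allocations out of sight. Here the intervention adds a lecture and four virtual sessions for one arm only, so an allocation is visible once it is acted on.

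What is at stake is selection bias at enrolment. A recruiter who can tell the next assignment may, even without intending to, invite or hold back a couple according to how keen on early parenthood they seem. Childbearing intention and planned pregnancy are primary outcomes, and the data come from questionnaires that participants complete themselves. Allocation concealment is therefore one of the few protections left, and the block rule should not weaken it without need.

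**Working it through.** **1. The plan's own figures.** 110 × 4 = 440 (Tehran); 50 × 4 = 200 (each of four other cities); 440 + 4 × 200 = 1240. These agree with the stated total and confirm a constant size of 4.

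**2. Certain predictions for a full observer** (knows the block size and sees every earlier allocation on the city list). A 2+2 block has six equally likely orders. In AABB and BBAA positions 3 and 4 are forced; in the other four orders only position 4 is.

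- Forced positions: 2 × 2 + 4 × 1 = 8 of 6 × 4 = 24, that is 1/3.
- Couples: 1240/3 ≈ 413; Tehran 440/3 ≈ 147; each other city 200/3 ≈ 67.
- For a 1:1 block of size b the share is 1/(b/2 + 1): 33.3% for 4, 25% for 6, 20% for 8. A larger but still fixed block helps only modestly.

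**3. Best guess for the same observer.** Chance of being right at positions 1 to 4:

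- position 1: 1/2
- position 2: 2/3
- position 3: (1/3) × 1 + (2/3) × 1/2 = 2/3
- position 4: 1

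The mean is (1/2 + 2/3 + 2/3 + 1)/4 = 17/24 = 70.8%, against 50% by chance.

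**4. An observer who sees only one centre.** Assumptions, not in the article: couples spread evenly and at random over a city's centres, and the envelope number shows the place in the block. Each earlier slot is then seen with probability p = 1/(number of centres). Certainty requires having seen both earlier allocations to the same arm, which has probability p². The share is (p²/3 + p²)/4 = p²/3.

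| Centres in city | Certain share | Cities | Couples |
|---|---|---|---|
| 1 | 1/3 = 33.3% | Shiraz (200) | 66.7 |
| 2 | 1/12 = 8.3% | Ahvaz, Tabriz (400) | 33.3 |
| 3 | 1/27 = 3.7% | Tehran, Mashhad (640) | 23.7 |
| All | 10.0% | 1240 | 123.7 |

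If envelopes were divided among centres in whole blocks of 4, the share would return to 1/3 at every centre.

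**5. Randomly varying sizes.** Simulated for a full observer who knows the set of sizes but not their order:

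| Block sizes | Certain | Best guess right |
|---|---|---|
| 4 fixed | 33.3% | 70.8% |
| 4, 6 | 5.4% | 69% |
| 4, 6, 8 | 2.2% | 68% |

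The gain is in certainty. Guessing from the running imbalance stays possible under any small balanced blocks.

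**The case against.** The case for leaving the plan alone is that most of the harm has to be inferred, and much of that stands.

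- **One third of allocations will be known.** A reader might infer this, but it is an upper bound. The article does not say that recruiters see the whole city sequence or know the block size, and publication of the size does not show that they knew it during enrolment. Nor does it say that those who enrol are those who teach. Sharing a city list between centres lowers what a single-centre recruiter can know. Shiraz is the exception, because there the centre's sequence is the city's sequence.
- **The allocation mechanism contradicts itself.** Also tempting, but not shown. The term central appears as the alternative to randomising centres as clusters, and can mean a centrally generated list for each city. List, assignment by the principal investigator and envelopes can form one chain. The description is unreconciled, which is less than a contradiction.
- **One numbered series cannot be run in order at several centres.** This assumes that the envelopes lie at the centres. The article does not say who holds or opens them, and a condensed article may leave custody to the full protocol. A single holder in each city could keep the order.
- **Consent already protects enrolment.** Ethical considerations requires written consent before randomisation. This limits steering after consent but not selective invitation beforehand.

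None of these points defends the constant block size. It is a stated rule, not an omission, and no reason is given for it.

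**Conclusion.** The concern holds in limited form. A constant block of 4 in a trial unblinded at field level is a stated choice that makes allocation more predictable than it need be. The share of assignments that could be known with certainty is about 10% (124 couples) if staff see only their own centre, rising to 33% (413 couples) if they see the whole city list. Both figures assume that the block size is known; the lower one also needs the even-spread and visible-number assumptions. For Shiraz the figure is one third, about 67 of 200 couples, on either view.

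The documents do not show that anyone would have or use this knowledge, so this is an avoidable risk and not a demonstrated bias. It merits a change because the change is cheap. The unclear mechanism is a request for clarification and does not carry the point.

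**What to change.** Generate the five city lists with randomly varying block sizes, for example 4, 6 and 8, and do not disclose the sizes or their order to city staff. Replace the sentence giving block size 4 and the two sentences giving block counts accordingly.

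Add one sentence saying how central randomisation, assignment by the principal investigator and the numbered envelopes work together where centres share a city list. Do not move to one list per centre unless block sizes also vary: with blocks still at 4, that would give a centre-level observer one-third certainty at all 11 centres (3 + 2 + 1 + 2 + 3).

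Cost: new computer-generated lists. Because 440 and 200 are multiples of 4, the present lists end balanced; with blocks up to 8, a list cut at its target can end at most 4 couples out of balance. If all five cities erred in the same direction, the difference would be 5 × 4 = 20 couples, or 630 against 610. The relative efficiency is (630 × 610)/(620 × 620) = 0.9997, so the loss of precision is negligible. A phone or online release system is not needed for this change and would carry its own cost.

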### Blinding

Given the nature of the intervention, it is not possible to blind participants to researchers involved in providing the intervention and data collection. However, allocation to intervention or control groups will be blinded for researchers in the data set available during the data analysis. To avoid the potential contamination between two groups, we will provide the educational intervention after the typical premarital counselling.

### Statistical method

Categorical variables will be presented by frequency (%), and quantitative variables will be reported as means (SD) or medians (with 25th to 75th quartiles), as appropriate. Graphical approach, numerical indices and the Shapiro-Wilk test will be used to evaluate the normality distribution and Leven test for homogeneity of variances in quantitative variables, respectively.

Comparisons between groups at baseline will be performed using Chi-square or Fisher-exact test for categorical variables, Independent samples t-test for normally distributed quantitative variables and Mann–Whitney U test for non-normally distributed quantitative variables. To compare the outcomes between the two groups over the time, repeated measures ANOVA will be used. Data will be analyzed using the SPSS software version 22 (IBM Corp. IBM SPSS Statistics for Windows, Armonk, NY, USA). For all analyses, a *P* value < 0·05 will be considered statistically significant.

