### Data collection

Data will be collected by questionnaires at baseline and 3, 12 and 18 months after the intervention in each selected city (Table 1). The post-test questionnaires will be completed by the participants through online forms. The participants’ phone number, email address and social network’s ID (WhatsApp) will be asked in order to send the post-test questionnaire links and some virtual educational materials.

In each city, two research collaborators will cooperate with the principal investigator. They will be introduced by the Ministry of Health and Medical Education, associated office for premarital counselling courses in all provinces. We will have a training session for these research staff and they will be justified about the study aims and procedure of data collection as well as educational intervention. They need to be in close contract with the principal investigator.

To minimize loss to follow up, we will provide an incentive to the eligible participants (A gift voucher for free sexual and reproductive health counselling) on the completion of the survey which may increase response rates. Four reminder emails or text messages will send out to non-respondents at one, two, three, and 4 weeks; a fifth telephone reminder was also undertaken.

Since a recent study in Iran showed an average interval between marriage and first pregnancy as about 15.4 ± 0.2 months in Iran [24], we are planning to follow the participants for occurrence of planned pregnancy about 18 months after the intervention.

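### Baseline fertility knowledge enters the planned repeated measures ANOVA only as an outcome level, never as a covariate, which costs efficiency by an amount that depends on an unstated correlation

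*Protocol article*

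**What the plan says.** Under Data collection, "Data will be collected by questionnaires at baseline and 3, 12 and 18 months after the intervention in each selected city". Table 1 marks fertility knowledge for assessment before the intervention and at each follow-up.

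The Sample size section rests on "fertility knowledge and intention toward childbearing that are important to be measured 3 months after the intervention". It takes a standardised difference of 0.2, "with a type I error of 5"% and "a type II error of 10"%, from which "sample size obtained 527 in each group", raised to 620 couples per group for 15% loss to follow-up. A second calculation in that section, for the comparison over time, names the levels as baseline, 3, 12 and 18 months and arrives at 660 couples in total.

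The Statistical method section states the outcome analysis in one sentence: "To compare the outcomes between the two groups over the time, repeated measures ANOVA will be used". The only other stated use of baseline data is a test of balance: "Comparisons between groups at baseline will be performed using Chi-square or Fisher-exact test for categorical variables", with t-tests or Mann–Whitney tests for quantitative variables. No section names the baseline score as a covariate.

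**The concern.** In a randomised trial, the baseline value of the outcome usually predicts the follow-up value, so adjusting for it removes variance at no cost in recruitment. A repeated measures ANOVA with baseline as an outcome level uses that information less well, in two ways:

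- **Group main effect.** It averages over all four occasions, including one where randomisation makes the expected difference zero. The effect is diluted.
- **Group-by-time term.** It measures departures from a constant group difference. Its baseline to 3-month component is a difference in change scores, with variance proportional to 2(1 − rho). Adjustment gives 1 − rho². The gap is 2(1 − rho) − (1 − rho²) = (1 − rho)², so with equal variances adjustment is never worse and is strictly better for rho below 1.

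What is at stake is the power and precision of the 3-month knowledge result, the result the trial is sized on. A chance imbalance in baseline knowledge is a lesser issue. The plan tests for it, but a significance test does not correct anything, and a change contrast over-corrects when rho is below 1.

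**Working it through.** **Inputs from the Sample size section:** d = 0.2, alpha 0.05 (sidedness not stated), power 90%, 527 per group before loss, 1:1 allocation.

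**Assumption:** rho between baseline and follow-up scores is not given. It is shown at 0.3, 0.5 and 0.7.

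**1. The plan's own figures.** A two-sided, unadjusted two-sample t-test with d = 0.2 and 527 per group has noncentrality 0.2 × √(527/2) = 3.247 and power 90.0%. At 526 it is just below 90%, so 527 reproduces. A one-sided test would need about 429, which does not match. 527/0.85 = 620 reproduces the loss adjustment. The 660 total reproduces as a between-groups F test in a repeated measures ANOVA with f = 0.1 (d = 0.2), four measurements, 90% power and rho = 0.5. That suggests 0.5 was the value used, but the protocol does not say so.

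**2. Baseline-adjusted 3-month comparison.** Noncentrality = 3.247/√(1 − rho²):
- rho 0.3: 3.247/0.954 = 3.40
- rho 0.5: 3.247/0.866 = 3.75
- rho 0.7: 3.247/0.714 = 4.55

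**3. Planned repeated measures ANOVA.** Assume compound symmetry and group differences of 0, 0.2, 0.2, 0.2 SD at the four occasions (mean 0.15).
- *Group-by-time*, 3 and 3 × 1,052 = 3,156 df. The squared deviations from the mean sum to 0.15² + 3 × 0.05² = 0.030. Lambda = (527/2) × 0.030/(1 − rho) = 7.905/(1 − rho), giving 11.29, 15.81 and 26.35.
- *Group main effect*, 1 and 1,052 df. Lambda = (527/2) × 0.15²/[(1 + 3 rho)/4], giving 12.48, 9.49 and 7.65.

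**4. Power, 527 per group**

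| | rho 0.3 | rho 0.5 | rho 0.7 |
|---|---|---|---|
| 3-month, adjusted for baseline | 92.5% | 96.3% | 99.5% |
| 3-month, unadjusted | 90.0% | 90.0% | 90.0% |
| Planned group-by-time test | 81.5% | 93.1% | 99.5% |
| Planned group main effect | 94.2% | 86.8% | 78.9% |
| Adjusted minus group-by-time | 11.0 | 3.2 | 0.0 |
| Adjusted minus main effect | −1.7 | 9.5 | 20.6 |

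At rho = 0.3 the main effect is slightly ahead, because it pools three follow-ups that are all assumed to carry the full effect.

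**5. Sensitivity to the effect pattern.** If the effect is 0.2 SD at 3 months and halves to 0.1 at 12 and 18 months, group-by-time power is 62.4%, 78.4% and 95.4%, and main-effect power is 65.3%, 53.6% and 45.3%. The adjusted 3-month figures do not change.

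**The case against.** **Baseline is not ignored.** As a repeated level, it already contributes to the group-by-time term. This stands: the complaint is about how efficiently it is used.

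**A single headline loss is tempting but unsupported.** A reader might infer that the plan gives up about 6 points of power. That is 96.3% less 90.0% at rho = 0.5, and it compares adjustment with the unadjusted t-test that sized the trial. The Statistical method section does not plan that t-test for outcomes. Against the planned group-by-time test the loss at rho = 0.5 is 3.2 points, and it runs from about 11 to 0 over the range shown. The protocol states no correlation that would fix one figure.

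**The plan reaches its stated power on its own terms.** An unadjusted 3-month comparison with 527 per group has 90.0%. Sizing without adjustment is conservative, not wrong. This stands too.

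**The unit of analysis is open.** The 527 are couples, both partners are recruited, and CFKS is scored per participant. A reader might divide by the stated design effect of 1.5 (527/1.5 = 351 per group) and claim a rise from 75.4% to 86.3% at rho = 0.5. That holds only with one score per couple and the design effect applied on top. With both partners analysed, 1,054/1.5 = 703 per group gives 96.3% unadjusted and 99.1% adjusted. The protocol does not settle which applies.

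**Covariates are often left to an analysis plan, and this is a condensed article.** True of a covariate list. But the article names the method and places baseline among its outcome levels, so the point concerns a stated choice.

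**Conclusion.** The point holds as a loss of efficiency, and the change should be made. It is not a validity error, and the stated sample size is not wrong on this account.

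With 527 per group and d = 0.2, the adjusted 3-month comparison exceeds the planned group-by-time test by about 11, 3 and 0 points at rho 0.3, 0.5 and 0.7. It exceeds an unadjusted 3-month comparison by 2.5, 6.3 and 9.5 points. These figures assume a two-sided test, one score per couple with no design effect, equal variances, compound symmetry and, for the planned ANOVA, a constant 0.2 SD effect at all three follow-ups. The direction against a change-score contrast holds for any rho below 1. The size depends on a correlation the protocol does not give.

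**What to change.** In the Statistical method section, state that the primary analysis of fertility knowledge is the 3-month between-group difference in CFKS percent-correct score, adjusted for baseline CFKS score. Use the same covariate for the 12- and 18-month scores. For childbearing-intention items analysed on a numeric scale, adjust for their own baseline value.

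State whether one or both partners' scores are analysed. If both, use a mixed model with a couple random effect, or couple-clustered standard errors. A plain linear model on participant scores would treat partners as independent.

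Do not rely on baseline significance tests to deal with imbalance.

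The cost is analysis wording, with no new data, visits or participants. The small downside is that a simple rule is needed for missing baseline scores, such as mean imputation of the covariate.

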**Methods:**

This study is a parallel randomised clinical trial with pre-test/post-test design. We will recruit 1240 marrying couples referring for compulsory premarital counselling in public health centers through stratified sampling in five metropolitan cities of Iran. The intervention group will receive both the typical premarital counselling training and a fertility knowledge package containing verbal and virtual educational package at five time episodes (one verbal session and four virtual sessions) within 4 weeks. The primary outcomes are fertility knowledge, childbearing intention and the first planned pregnancy rate (positive pregnancy test) and the secondary outcomes include contraception method use, miscarriage and unplanned pregnancy. Participants will respond to a self-administered demographic/reproductive characteristics questionnaire, the Cardiff Fertility Knowledge Scale (CFKS) and the childbearing intention questionnaire.

Data will be collected through online questionnaires at baseline and 3, 12 and 18 months after the intervention. Data will be analyzed using Chi-square or Fisher-exact test for categorical variables, Independent sample t-test for normally distributed quantitative variables and Mann–Whitney U test for non-normally distributed quantitative variables. To compare the outcomes between the two groups over the time, repeated measures ANOVA will be used. We hypothesize that the positive impact of increasing the fertility knowledge is the reduced involuntarily childlessness.

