### Outcomes

The primary outcomes are fertility knowledge, childbearing intention and the first planned pregnancy rate (positive pregnancy test).

The secondary outcomes include the contraception method use, miscarriage and unplanned pregnancy.

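### The Statistical method section sends binary and nominal outcomes, including the primary outcome first planned pregnancy, to repeated measures ANOVA, and conflicts with the Abstract and Sample size sections

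*Protocol article*

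**What the plan says.** **Outcome types (Outcomes section).** "The primary outcomes are fertility knowledge, childbearing intention and the first planned pregnancy rate (positive pregnancy test". The next sentence reads "The secondary outcomes include the contraception method use, miscarriage and unplanned pregnancy". First planned pregnancy, miscarriage and unplanned pregnancy are each yes or no for a couple. Contraception method is a set of unordered categories.

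**Methods (Statistical method section).** The categorical tests are tied to one time point: "Comparisons between groups at baseline will be performed using Chi-square or Fisher-exact test for categorical variables". The t-test and Mann–Whitney test stand in the same baseline sentence. The next sentence covers everything after baseline: "To compare the outcomes between the two groups over the time, repeated measures ANOVA will be used". It does not separate scores from events.

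**Abstract, Methods.** "Data will be analyzed using Chi-square or Fisher-exact test for categorical variables", here without any limit to baseline. The Abstract also names repeated measures ANOVA for comparing outcomes over time.

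**Sample size section.** The calculation based on repeated measures ANOVA is described as being for quantitative outcomes across the four assessments.

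**Timing (Data collection section).** Questionnaires are given "at baseline and 3, 12 and 18 months after the intervention in each selected city".

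**The concern.** Planned pregnancy is the outcome the Background relies on to show whether knowledge turns into childbearing behaviour, and the Discussion hopes the results will inform government policy. The section that governs the analysis gives this outcome a method built for repeated quantitative measurements. The article does not leave the matter open for a later plan; it names a method, and the method does not suit four of the six listed outcomes.

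Two things are at stake. First, the pregnancy result could be reported as an F test with no effect size a policy reader can use. Second, because three sections point in different directions, the test for a primary outcome could be chosen after the data are seen and still be called consistent with the protocol.

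**Working it through.** **1. The three places side by side**

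| Place | Chi-square/Fisher | Repeated measures ANOVA |
|---|---|---|
| Statistical method | baseline comparisons only | the outcomes, no exception |
| Abstract, Methods | categorical variables, no time limit | the outcomes, no exception |
| Sample size | not mentioned | quantitative outcomes |

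No section assigns the categorical outcomes a follow-up analysis with a time point and an effect measure. The Statistical method section, read alone, assigns them ANOVA.

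**2. Contraception method.** Its categories have no order or distance. A mean of category codes changes with the coding, so an ANOVA on it has no meaning.

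**3. First planned pregnancy.** Take cumulative status as 0/1 at months 0, 3, 12 and 18. The event happens at most once, so status never returns to 0. The documents give no pregnancy rate, so rates are assumed: 0, 5, 25 and 40%, the same in both arms, with baseline zero also an assumption.

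Uncorrected repeated measures ANOVA needs the variance of the difference between any two time points to be equal (sphericity). For a status that only rises, Var(later − earlier) = q(1 − q), where q is the rise in the cumulative rate:

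- months 0 to 3: 0.05 × 0.95 = 0.0475
- months 3 to 12: 0.20 × 0.80 = 0.1600
- months 12 to 18: 0.15 × 0.85 = 0.1275
- months 0 to 18: 0.40 × 0.60 = 0.2400

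The largest is about five times the smallest (0.2400 / 0.0475 = 5.1). Sphericity fails because of the kind of outcome, not by chance.

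**4. Effect on the error rate.** The simulation used 527 couples per arm, 3000 trials per scenario, and no true effect. The 527 is the Sample size section's evaluable number. It reproduces for a two-sided t-test with d = 0.2, alpha 0.05 and 90% power (noncentral t power at 527 is 0.9004), and 527 / 0.85 = 620.

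| Assumed cumulative rates, both arms | Group-by-time, uncorrected | Group-by-time, Greenhouse–Geisser | Chi-square at 18 months | Mean epsilon |
|---|---|---|---|---|
| 0/5/25/40% | 6.8% | 4.5% | 5.0% | 0.65 |
| 0/2/10/20% | 7.8% | 5.2% | 5.0% | 0.60 |

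The Monte Carlo standard error at 5% is √(0.05 × 0.95 / 3000) = 0.4 points, so the uncorrected excess is real but modest. Repeat runs, including one with higher assumed rates, put the uncorrected test at about 6–7.4% and the corrected test at 4.2–4.9%. The article names no sphericity correction.

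**5. What the F test reports.** Neither the group effect nor the group-by-time effect is a risk difference or risk ratio at 18 months, the horizon the Data collection section sets for planned pregnancy.

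**The case against.** **Loose drafting.** The best defence is that the authors meant ANOVA for the scores. The Sample size section says quantitative, the Abstract lists chi-square and Fisher tests without a baseline limit, and the Statistical method section reports categorical variables as frequencies. This is quite likely the intent, and it stands as a limit on the criticism: the charge is conflicting text, not a proven decision to run ANOVA on pregnancy. It does not remove the conflict. The Abstract also sends the outcomes over time to ANOVA, and the governing section makes no exception.

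**An invalid test.** A reader might infer that ANOVA cannot validly test a binary outcome. That goes too far. With equal arms of this size, the sphericity-corrected test roughly keeps its level (step 4 above). Only the nominal outcome is beyond rescue.

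**A halved effect.** A reader might infer that averaging over assessments dilutes the result. With assumed rates of 0/5/40/55% and 0/5/50/65%, the group main effect is (0 + 0 + 10 + 10) / 4 = 5 points against 10 at 18 months. But the variance of the average shrinks too. Simulated power on these rates was 0.90 for the main effect, 0.94–0.95 for the corrected group-by-time test and 0.91 for chi-square at 18 months. The problem is one of scale, with no meaningful loss of power.

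**Biased exposure time.** Follow-up is dated from the end of an intervention that lasts 4 weeks and is given to one arm. A reader might infer that the intervention arm has longer at risk. No section says so: Table 1 and the Data collection section give one schedule for both arms. What stands is that the control arm's time zero is ambiguous.

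**Details an article may omit.** How an unplanned pregnancy counts as a competing event can be left to a fuller document. That the sample size rests on knowledge and intention is stated openly and is a separate matter.

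**Conclusion.** The point holds as a conflict and a misassigned method. Read literally, the Statistical method section gives one primary and three secondary categorical outcomes to repeated measures ANOVA, while the Abstract and Sample size sections point to a narrower use.

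The consequences differ by outcome. For contraception method, ANOVA is unsuitable. For the three binary outcomes the main loss is an interpretable effect estimate. In addition, the uncorrected group-by-time test for planned pregnancy is modestly anti-conservative, at about 6–8% against 5%. That range rests on assumed cumulative rates, an assumed zero baseline and 527 evaluable couples per arm. The text conflict and the unsuitability for a nominal outcome rest on no assumption.

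The documents do not support a claim of a halved treatment effect, of an established exposure bias in favour of the intervention, or of a test that is invalid under any handling.

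**What to change.** - In the Statistical method section, restrict repeated measures ANOVA to the knowledge and intention scores, and align the Abstract and Sample size wording with this.
- For first planned pregnancy, compare the proportion of randomised couples with the event by 18 months as a risk difference or risk ratio with 95% CI, stratified by city, since city is the randomisation stratum. A Mantel–Haenszel estimate or a city-adjusted binomial model would serve.
- Use logistic models for miscarriage and unplanned pregnancy, and a multinomial model for contraception method.
- Count follow-up from randomisation in both arms, so that the control arm has a defined time zero.

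The cost is wording and a little analysis work. Sample size, randomisation and the number of assessments are unaffected.
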